## Abstract

**Background:**

Healthcare workers (HCWs), such as doctors, nurses, and support staffs involved in direct or indirect patient care, are at increased risk of influenza virus infections due to occupational exposures. Vaccination is the most effective way to prevent influenza. Despite the World Health Organization (WHO) recommendations, Bangladesh lacks a seasonal influenza vaccination policy for HCWs, and thus vaccination rates remain low. The current project aims to investigate the effect of interventions on influenza vaccine awareness and availability of vaccine supply, explore HCWs’ knowledge and perceptions about influenza vaccination, understand the barriers and motivators for influenza vaccine uptake, and understand policymakers' views on the practicality of influenza vaccination among HCWs.

**Method:**

We will conduct the study at four tertiary care teaching hospitals in Bangladesh, using a cluster randomized controlled trial approach, with the hospital as the unit of randomization and intervention. The study population will include all types of HCWs.The four different types of intervention will be randomly allocated and implemented in four study hospitals separately. The four interventions will be: i) ensuring the availability of influenza vaccine supply; ii) developing influenza vaccine awareness; iii) both ensuring influenza vaccine supply and developing influenza vaccine awareness and iv) control arm with no intervention. Both quantitative and qualitative approaches will be applied to assess the intervention effect. We will estimate the Difference in Differences (DID) with 95% CI of the proportion of vaccine uptake between each intervention and control (non-intervention) arm, adjusting for the clustering effect. The qualitative data will be summarised using a framework matrix method.

**Discussion:**

The results of this study will inform the development and implementation of a context-specific strategy to enhance influenza vaccination rates among Bangladeshi HCWs.

**Trial registration:**

Clinicaltrials.gov NCT05521763. Version 2.0 was registered in September 2022, and the first participant enrolled in March 2022. Retrospectively registered.

**Supplementary Information:**

The online version contains supplementary material available at 10.1186/s12889-022-14182-w.

## Background

Influenza annually affects a considerable fraction of the world's population, causing significant health, social, and economic consequences [1]. Globally, influenza infects approximately 5–15% of adults, and an estimated range of 291,000 to 646,000 persons die from seasonal influenza-related respiratory illnesses each year [2–4]. Influenza causes significant morbidity and mortality among healthcare workers (HCWs) due to occupational exposure [5–7]. After a comprehensive assessment of 26 research and a meta-analysis of 15 trials, Lietz et al. found that HCWs had an influenza prevalence of 6.3%, significantly higher than healthy working adults (5.1%) [7, 8]. During reported influenza outbreaks, the attack rate among HCWs ranged between 18% and 24%, higher than the general population (11%) [9, 10]. HCWs often work while experiencing influenza-like illness (ILI) (40–83%), increasing the likelihood of influenza transmission to colleagues and patients [6, 11].

Influenza vaccines are the most effective way to prevent infection and reduce the severity of the disease [12, 13]. Retrospective studies have shown correlations between increased influenza vaccination among HCWs and decreased nosocomial influenza in acute care settings [14–16]. Considering the disease burden of influenza, in 2012, the World Health Organization’s (WHO) Strategic Advisory Group of Experts (SAGE) on immunization recommended influenza vaccination for HCWs [17]. WHO SAGE declared HCWs as the highest priority risk group [18, 19].

Despite WHO vaccine recommendations and rising scientific data on influenza burden and awareness, vaccination coverage rates among HCWs in low- and middle-income countries (LMICs) continued to be low [18, 20, 21]. Moreover, less than half (46%; 64/138) of LMICs have national policies for seasonal influenza vaccination for HCWs [21]. Persistently low vaccination rates among HCWs in most LMICs raise international concerns about the broader spread of influenza to patients, particularly those at increased risk of influenza-like illness [1, 22, 23].

Studies have shown that interventions such as resources for education and training (e.g. posters, mass mailings, leaflets, newsletters, seminars, lectures, demonstrations, expert visits, and multimedia) enhance awareness and understanding of the influenza vaccine and improve vaccine uptake among HCWs [24]. Healthcare workers can also boost influenza vaccine uptake by offering incentives for vaccination, organizing campaigns to enhance vaccine knowledge, issuing vaccination reminders, and using lead vaccine advocates [24]. A cluster randomized controlled trial among healthcare workers of 33 Dutch nursing homes conducted in 2010 demonstrated that over the course of one influenza season, adopting education and institutional support increased vaccination uptake in the intervention group to 25%, whereas it was 16% in the control group [25].

Comprehensive reviews on the acceptance of the influenza vaccine by HCWs have identified several factors influencing vaccine uptake [26]. The primary motivations for HCWs’ influenza vaccination uptake were self-preservation and protecting family members avoiding sickness, or protecting patients [26]. At the same time, fear about vaccines’ safety, low-risk perception, refusal of the social benefit of the influenza shot, low social pressure, vaccination skepticism, not willingness to be flu-vaccinated, shortage of influenza-specific competence, and inaccessibility to get vaccination facilities were identified as a significant deterrent for vaccine uptake [26].

In Bangladesh, HCWs frequently reported hospital-acquired respiratory illnesses [27]. A study in Bangladeshi tertiary care hospitals found that 27% (61/226) of HCWs experienced a respiratory illness during the study period [27]. Each illness episode lasted an average of 4.3 days, resulting in a total of 27 days per HCW per year absent due to illness [27]. Moreover, with overcrowded hospitals and a lack of infection control practices, the nosocomial transmission of influenza would likely be amplified during a pandemic [28, 29]. This both escalates sickness absenteeism among the HCWs and reduces the workforce in the healthcare facilities [29].

There is currently no national influenza vaccination strategy in Bangladesh for the population at increased risk of influenza-like-illness such as HCWs, as recommended by WHO [30]. Each year, the Ministry of Health and Family Welfare (MoH&FW) of the People's Republic of Bangladesh provides free influenza vaccination to all Hajj pilgrims as a mandatory requirement imposed by the Saudi Health Ministry; this is the only group in Bangladesh that has a seasonal influenza vaccine policy [31]. Currently, only a few selected private vaccination centers in Dhaka offer influenza vaccines at a market-rated price (MRP). However, the number of doses administered per year by private vaccination centers remains unknown**.** Due to the limited availability of the vaccine in Bangladesh, the willingness to receive the influenza vaccine of risk group populations such as HCWs remains unclear.

To protect HCWs and reduce nosocomial influenza transmission in both epidemic and pandemic settings, the promotion of influenza vaccination for this risk group should be a priority. HCWs’ knowledge, attitudes, and perceptions about influenza and influenza vaccine influence their decision regarding vaccination. Understanding the barriers and motivation of vaccine uptake is required to tailor local influenza vaccination policies and implementation strategies to facilitate and improve vaccine uptake.

This study intends to determine the current status of influenza vaccination among HCWs and generate preliminary data on whether increased awareness and availability of influenza vaccine improve vaccine uptake and factors affecting the uptake rates. The critical data generated from the study would inform the development of an influenza vaccination policy for HCWs.

We hypothesize that increasing awareness and availability of influenza vaccine supply would increase influenza vaccine uptake among Bangladeshi HCWs. We formulated the research questions (RQ): What are the effects of influenza vaccination awareness or availability of vaccine supply or both in the study hospitals on HCWs' influenza vaccine uptake in Bangladesh?

## Methods

### Study setting

The study will be conducted at four out of twenty-five conveniently selected tertiary-level public teaching hospitals in Bangladesh [32]. We have chosen the study hospitals considering several factors. Firstly, to minimize the diffusion of interventions, we have chosen hospitals from four different administrative divisions (i.e. geographically distant). Secondly, we have avoided hospitals where we have other ongoing studies among HCWs. Lastly, we have chosen tertiary-level public hospitals with a relatively higher number of HCWs to meet the minimum sample size requirement per study arm. The name and locations of the hospitals are as follows (Fig. 1):Sylhet MAG Osmani Medical College Hospital, Sylhet, BangladeshRajshahi Medical College Hospital, Rajshahi, BangladeshKhulna Medical College Hospital, Khulna, BangladeshMymensingh Medical College Hospital, Mymensingh, Bangladesh

**Fig. 1 Fig1:**
[figure not shown]
Location of the study sites. Source: Authors generated the map using QGIS version 3.2.1

### Study design

We will use a cluster randomized controlled trial design with the hospital as the unit of randomization and intervention. The four different types of intervention will be randomly allocated and implemented in four study hospitals separately. The four interventions will be: 1^st^ intervention: ensuring availability of influenza vaccine supply; 2^nd^ intervention: developing influenza vaccine awareness activities; 3^rd^ intervention: both ensuring the availability of influenza vaccine supply and developing influenza vaccine awareness activities, and 4^th^ intervention: control arm with no intervention. We will assess influenza vaccine uptake before and after intervention and between different study arms. Moreover, barriers and motivators of vaccine uptake will be explored by applying both quantitative surveys and qualitative methods (i.e. in-depth interviews and focus group discussions)
. We will also use a qualitative approach (i.e. key informant interviews) to understand the policymakers’ (such as hospital administration, influenza vaccine expert) perspectives and opinions on influenza vaccine uptake among HCWs. Figure 2 & Fig. 3 illustrates the study design and interventions.

**Fig. 2 Fig2:**
[figure not shown]
Schematic diagram of study method

**Fig. 3 Fig3:**
[figure not shown]
HCWs information delivery mechanism on influenza vaccination

### Study population and participant recruitment

Our study population will be all types of HCWs (Supplementary Table 1) involved in patient care working at the study facilities at the time the study begins; HCWs will be broadly categorized into doctors, nurses, and allied health personnel (supplementary table 1). HCWs who will not be directly or indirectly involved in patient care, such as basic medical science faculties (e.g., anatomy, physiology, biochemistry, forensic medicine, pathology, and microbiology), will not be included as participants. All eligible HCWs who will be working at the study hospitals during the implementation period and consent to participate in the study will be enrolled in the study as participants. We will collect the list of HCWs currently working in the facility from the hospital administration. Our team will approach the randomly selected HCWs and invite them to participate in the study. Eligible HCWs who will consent will be enrolled.

### Sample size and sampling

#### Quantitative survey

Our primary outcome of interest is influenza vaccine uptake among HCWs. An ongoing study among HCWs in Bangladesh at tertiary level facilities has shown a baseline influenza vaccine uptake of about 5% ([name] et al., personal communication). But comprehensive reviews on influenza vaccine uptake among HCWs have identified a wide variation of vaccine uptake rates globally between 13–53% [26]. We expect a similar uptake rate between 10–50% following awareness and availability of influenza vaccine supply in study hospitals. However, we assume an increase in the uptake rate of at least five percentage points for the sample size requirement.

For a one-sided test, given the allocation ratio R = n_2_/n_1_, the total sample size n is computed by the following formula:$$n=\frac{{\left\{{z}_{1-\alpha \sqrt{\overline{p }\left(1-\overline{p }\right)}-{z}_{\beta }\sqrt{{w}_{2}{p}_{1}\left(1-{p}_{1}\right)+{w}_{1}{p}_{2}\left(1-{p}_{2}\right)}}\right\}}^{2}}{{w}_{1}{w}_{2}{\left({p}_{2}-{p}_{1}\right)}^{2}}$$

where uptake rate p_1_ = 5% in the control group and p_2_ = 10% in the intervention group, the pooled proportion $$, \overline{p }$$ = (n_1_p_1_ + n_2_p_2_)/(n_1_ + n_2_), and w_1_ = 1/(1 + R) and w_2_ = R/(1 + R). (Stata 13 manual; page 156). In our case, R = 1 for equal allocation, Z_1-α_ = 1.645 for 5% level of significance and Z_β_ = 0.84 for 80% power.

The estimated sample size is 435 HCWs in each arm. With a clustering (design) effect of 2 and a 10% non-response rate, a sample size of 957 HCWs is required for each arm. Consequently, the total sample size is 3,828.

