### Data analysis

#### Quantitative data

We will conduct descriptive analysis to summarise the categorical variables using frequency, percentage, and 95% confidence interval (CI). We will summarise numerical or continuous variables using mean and standard deviation (SD) for symmetric distribution and median and interquartile range (IQR) for asymmetric distribution. We will estimate the Difference in Differences (DID) with 95% CI of the proportion of vaccine uptake between each intervention and control (non-intervention) arm, adjusting for the clustering effect and testing whether it is statistically significant or not at a 5% level of significance. We will also look for association and estimate the odds ratio (OR)/risk ratio (RR) with 95%CI between influenza vaccine uptake and its barriers and motivators, adjusting for clustering effect and covariates using multiple logistic regression/multilevel models.

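### The stated one-sided inputs (1.645, 0.84) give 342 per arm, not 435; the printed 435 is the two-sided 5% result, so the one-sided wording is the part to correct

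*Protocol article*

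**What the plan says.** The Quantitative survey part of Sample size and sampling (protocol article) prints a two-proportion formula, all its inputs and its result.

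- Test: "For a one-sided test, given the allocation ratio R", with R = 1.
- Critical value: "1.645 for 5% level of significance".
- Power: "0.84 for 80% power".
- Rates: "5% in the control group" and "10% in the intervention group", in line with the sentence "we assume an increase in the uptake rate of at least five percentage points for the sample size requirement".
- Result: "The estimated sample size is 435 HCWs in each arm".

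A design effect of 2 and 10% non-response then bring the figure to 957 per arm and 3,828 over four arms.

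The Data analysis section (Quantitative data) plans a difference-in-differences estimate of uptake with a 95% confidence interval for each intervention arm against control, "testing whether it is statistically significant or not at a 5% level of significance". It does not say whether that test is one-sided or two-sided.

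**The concern.** The value 1.645 is the one-sided 5% quantile, so the words and the number in the sample size section agree with each other. The result does not follow from them: a one-sided 5% test with 80% power needs clearly fewer than 435 per arm at these rates.

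Two things are at stake. The recruitment target rests on 435, so as printed it is not supported by its own justification. In addition, the only explicit statement of sidedness in the article is one-sided, while the planned interval is a 95% interval, conventionally two-sided. If both were applied, a result with a one-sided p-value between 0.025 and 0.05 would be significant under one and would have an interval that includes zero under the other.

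**Working it through.** **Inputs** (all from the sample size section): p1 = 0.05, p2 = 0.10, R = 1, so w1 = w2 = 0.5 and the pooled proportion is 0.075; Z(1-α) = 1.645; Z(β) = 0.84 for 80% power.

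**Formula**, with the power term added to the critical-value term:

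total n = [z_a × √(0.075 × 0.925) + z_b × √(0.5 × 0.05 × 0.95 + 0.5 × 0.10 × 0.90)]² / (0.5 × 0.5 × 0.05²)

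The square roots are √0.069375 = 0.2634 and √0.06875 = 0.2622. The denominator is 0.000625.

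**1. Reproducing the printed 435.** Two-sided 5%, z_a = 1.96:
- With z_b = 0.8416: total 868.9, or 434.4 per arm, rounded up to **435**.
- With z_b rounded to 0.84: total 867.9, or 433.9 per arm, rounded up to 434. The last unit therefore depends on unrounded quantiles.

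**2. The inputs as stated.** One-sided 5%, z_a = 1.645:
- With z_b = 0.84: (0.4333 + 0.2202)² / 0.000625 = 683.4 in total, or 341.7 per arm, rounded up to **342**.
- With exact quantiles: 342.1 per arm, rounded up to **343**.

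**3. Other one-sided versions at 80% power.** Continuity-corrected 382, unpooled variance 340, arcsine 333. None is near 435, so neither rounding nor the choice of variance formula explains the gap. The shortfall is 435 − 343 = 92 per arm, which is 21% of 435.

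**4. Inflation, by the article's own rule (× 2 × 1.1).**

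| Basis | Per arm | After inflation | Four arms |
|---|---|---|---|
| Two-sided (matches print) | 435 | 957 | 3,828 |
| One-sided (as stated) | 343 | 754.6, so 755 | 3,020 |

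The difference in total is 3,828 − 3,020 = 808.

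**5. Power of the simple two-group comparison.** Power = Φ{[0.05√n − z_a × √(2 × 0.069375)] / √(0.0475 + 0.09)}:
- n = 435, two-sided: Φ(0.843) = 80.1%.
- n = 435, one-sided: Φ(1.160) = 87.7%.
- n = 343, two-sided: Φ(0.528) = 70.1%.

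**6. Sign of the power term.** The formula subtracts the z(β) term while the text gives z(β) as +0.84. A minus sign requires the lower quantile, −0.84.

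**The case against.** Several points on the other side are fair.

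- The hypothesis in the Background is directional (uptake is expected to rise), so planning with a one-sided test is not improper in itself. This stands, but it does not make 1.645 yield 435.
- The printed target is the larger of the two, so no power is lost if recruitment follows it. This also stands and limits the practical weight of the point.
- The analysis section never mentions one-sided testing. It leaves sidedness unstated, so the conflict with it is inferred from the 95% interval and is not printed.

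A reader might infer more than the documents support:

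- *That the test, the sample size and the interval all contradict one another.* They do not: 435 and a two-sided 95% interval agree, and only the one-sided wording with 1.645 is out of line.
- *That the trial plans to claim significance one-sidedly.* Nothing in the analysis section says so.
- *That the minus sign implies a far smaller trial.* Taken literally it gives a total of about 73, but 435 plainly did not come from that reading, and the formula's layout is damaged in the text at hand. This is a slip of sign convention only.
- *That 435 is thereby shown to be enough for the planned analysis.* The check covers the simple two-proportion formula only.

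**Conclusion.** The point holds as an inconsistency between the stated test and the stated sample size. The stated inputs give 342 per arm (343 with exact quantiles); 435 is the two-sided 5% result. Nothing elsewhere in the article resolves the difference. Carried through like for like, it is worth 808 participants in total (3,020 against 3,828), or a nominal power of 88% rather than 80% at 435 effective per arm.

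That the two-sided reading is the intended one is an inference, drawn from the match with 435 and from the planned 95% interval. The size of the gap rests on the article's own rates, power, design effect and multiplication by 1.1. The point should be corrected, but it concerns reporting and the definition of the test, and on the two-sided reading it gives no reason to alter recruitment.

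**What to change.** In the sample size section, describe the test as two-sided and replace Z(1-α) = 1.645 by Z(1-α/2) = 1.96. Either quote z(β) as −0.84 or put a plus sign in the formula. Note that unrounded quantiles were used, because 1.96 with 0.84 gives 434. In the Data analysis section, state that the 5% level is two-sided.

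This costs a few words. The figures 435, 957 and 3,828 then follow from the stated inputs. If a one-sided test really is intended, the sample size figures must be recomputed, and the analysis section must state the one-sided level and an interval that matches it. Neither version settles whether a simple two-proportion formula suits the clustered difference-in-differences analysis.

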### Quantitative data collection

We will employ a quantitative method for evaluating the effect of the intervention. We will perform the following activities:

5.1. We will conduct a baseline survey among HCWs of the study hospitals to collect information on HCWs’ influenza vaccine uptake history and their knowledge and perception of influenza vaccination.

5.2 At the end of the influenza vaccine season, we will do a post-intervention survey at study facilities to collect similar information.

Trained staff will approach the participants to solicit their interest and consent. The staff will be well-spoken and discuss with the study participants regarding confidentiality, objectives of the survey, use of data, and utility of results. Those who agree to participate will be interviewed according to the survey questionnaire. The structured questionnaire will be developed and contextualized following a review of the literature from prior research [40–44]. The questionnaire will be focused on the number of vaccinated HCWs (evidence from the signed vaccination card), socio-demographic information of the participants, including age, gender, profession (doctor/nurse), and department; perception of influenza risk; perception of vaccine effectiveness and side effects, practices of recommending vaccination to family and patients, and practice and attitude towards a mandatory vaccination and their willingness to pay for future vaccination.

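### The sample size is derived for a single 5% v 10% comparison, but the planned analysis is a difference in differences, so the stated 80% power does not apply to it

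*Protocol article*

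**What the plan says.** **Sample size and sampling, Quantitative survey.** The outcome is fixed first: "Our primary outcome of interest is influenza vaccine uptake among HCWs". An ongoing study among Bangladeshi HCWs "has shown a baseline influenza vaccine uptake of about 5" per cent. For the effect, "we assume an increase in the uptake rate of at least five percentage points for the sample size requirement". The calculation is introduced with "For a one-sided test, given the allocation ratio R", and the rates entered are "5% in the control group and p_2_ = 10% in the intervention group", with z-values of 1.645 and 0.84. The result is "The estimated sample size is 435 HCWs in each arm". A design effect of 2 and 10% non-response bring it to 957 per arm, or 3,828 over four arms.

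**Data analysis, Quantitative data.** The between-arm analysis of uptake is different: "We will estimate the Difference in Differences (DID) with 95% CI of the proportion of vaccine uptake between each intervention and control (non-intervention) arm". It is adjusted for clustering and tested at the 5% level, with no side given. The abstract names the same estimator.

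**Quantitative data collection, items 5.1 and 5.2.** A baseline survey is followed at the end of the season by a second one: "we will do a post-intervention survey at study facilities to collect similar information". The text does not say whether the second survey covers the same HCWs.

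**The concern.** The sample-size formula contains two estimated proportions, one per arm, at one time. A DID contains four: baseline and post-intervention uptake in each of two arms. The sampling error of both baseline surveys therefore enters the estimate. It is offset only to the extent that a person's baseline and follow-up answers are correlated, which requires the same people to be interviewed twice. The calculation has neither the baseline terms nor such a correlation.

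The results are meant to inform national vaccination policy. A DID whose interval includes zero could be read as the outcome of a test with 80% power for five points, when the planned analysis may have had appreciably less.

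**Working it through.** **Inputs from the protocol:** baseline and control uptake 0.05; intervention uptake 0.10; 435 per arm before inflation; design effect 2; non-response 10%; 5% level; 80% power.

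**Assumptions the protocol does not state:** control stays at 5% and intervention goes from 5% to 10%; 957 is the number per arm in *each* round; the design effect of 2 carries over to the DID. The effective number is then 957 / 1.1 / 2 = 435 per arm per round.

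**1. The plan's own figure.** With p̄ = 0.075, n per arm = [z_α√(2 × 0.075 × 0.925) + 0.84√(0.0475 + 0.09)]² / 0.05².

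- z_α = 1.96: (0.7301 + 0.3115)² / 0.0025 = 434, or 435 with unrounded z-values.
- z_α = 1.645, as stated: (0.6128 + 0.3115)² / 0.0025 = 342, or 343 with unrounded z-values.

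So 435 is the two-sided answer, although the text calls the test one-sided. The inflation reproduces: 435 × 2 × 1.1 = 957, and 957 × 4 = 3,828.

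**2. Variance of the two estimators** (numerator, to be divided by n).

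- Single comparison: 0.0475 + 0.09 = 0.1375.
- DID, independent rounds: 3 × 0.0475 + 0.09 = 0.2325, which is 1.69 times as large.
- DID, same HCWs, correlation r: V = 0.2325 − 2r × 0.0475 − 2r√(0.0475 × 0.09) = 0.2325 − 0.2258r.

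**3. Power for a 5-point DID at 435 per arm per round.** Power = Φ(0.05/√(V/435) − z_α). For independent rounds, SE = √(0.2325/435) = 0.0231 and 0.05/SE = 2.163. This gives Φ(2.163 − 1.96) = 58.0% two-sided and Φ(2.163 − 1.645) = 69.8% one-sided.

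| Pre-post correlation | V | Two-sided power | One-sided power |
|---|---|---|---|
| 0 (independent rounds) | 0.2325 | 58.0% | 69.8% |
| 0.1 | 0.2099 | 62.4% | 73.6% |
| 0.2 | 0.1873 | 67.3% | 77.8% |
| 0.3 | 0.1648 | 72.9% | 82.2% |
| 0.4 | 0.1422 | 79.0% | 86.9% |
| 0.5 | 0.1196 | 85.4% | 91.5% |

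Power reaches 80% at r of about 0.42 two-sided and about 0.25 one-sided.

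**4. Detectable DID, independent rounds, two-sided.** Solve d = (1.96 + 0.84)√{[3 × 0.0475 + (0.05 + d)(0.95 − d)]/435}. The solution is d ≈ 0.0666, about 6.7 points.

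**5. Size for 80% power at 5 points, independent rounds.** n = (z_α + 0.84)² × 0.2325 / 0.0025. This is about 730 effective per arm per round two-sided (× 2 × 1.1 ≈ 1,606) or 575 one-sided (≈ 1,265), against 435 (957).

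**6. Sensitivity to the other two assumptions, independent rounds.**

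- If 957 covered both rounds together (about 217 effective per round), power would be 33% two-sided or 45% one-sided.
- If a constant hospital effect cancelled in the DID and the design effect were 1 (870 per round), SE = √(0.2325/870) = 0.0163 and two-sided power would be about 86%.

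**The case against.** A reader might infer that the trial simply has 58% power rather than 80%. The documents do not support that flat statement, for four reasons.

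- **Independent rounds are not stated.** Several features lean towards one enrolled group. The population is defined as staff in post when the study begins, vaccination cards carry a unique number in arms 1 to 3, and a single total of 3,828 is given. This is suggestive only: no cards are described for the control arm, and the study schematic is not visible. With re-interview and a correlation of 0.42 or more there would be no two-sided shortfall.
- **The side of the test is open.** The sample-size text says one-sided and the analysis text gives no side. One-sided, the independent-rounds figure is 70%.
- **957 is given per arm, not per round.** The per-round reading is an assumption.
- **The design effect may not carry over.** A stable difference between hospitals cancels in a DID, and with a design effect of 1 power would be about 86%.

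It can also be said that five points is a floor and that the protocol expects uptake of 10–50%, so 6.7 points lies near the bottom of the expected range.

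All of this stands as a limit on the number. None of it restores the stated 80%, which is attached to five points and rests on a calculation that does not involve a DID. Recovering 80% requires an assumption about pairing, correlation, side or design effect that the power paragraph does not make. A separate analysis plan would not remove the mismatch, because the protocol itself states both the calculation and the estimator.

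**Conclusion.** The point holds in conditional form. The sample size is derived for a single post-intervention comparison, the stated effect analysis is a DID, and the 80% power does not apply to that analysis.

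For a 5-point DID, with a design effect of 2 and 435 effective HCWs per arm in each round, power is about 58% two-sided or 70% one-sided for independent surveys. It rises to 79–85% two-sided if the same HCWs are re-interviewed with a correlation of 0.4 to 0.5. The documents do not settle which case applies, so neither 58% nor 80% should be quoted as the power of the trial.

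There is a further limit. With one hospital per arm, between-hospital variation in *change* cannot be estimated from the data, so every figure here is conditional on the assumed design effect.

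**What to change.** Rewrite the power paragraph for the DID estimator, stating:

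- whether the two rounds are independent samples or the same HCWs;
- the side of the DID test, reconciled with the calculation (435 is the two-sided result; the stated 1.645 gives about 343);
- that 957 is the number per arm per round, if that is meant;
- the assumed pre-post correlation and design effect, with a note that one hospital per arm gives no means of checking the latter for change over time.

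Give power as the conditional range above, and do not quote 80% for a 5-point DID unless the stated assumptions support it. This costs rewording only and needs no extra participants.

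If the same HCWs are interviewed twice, analyse the paired change and allow for loss between rounds, which the 10% non-response allowance is not described as covering. This choice has a real cost: the same staff must be followed up, and an identifier must be kept across rounds in all four hospitals, including the control hospital, for which no card is described.

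### The 10% non-response allowance is applied as × 1.1 instead of ÷ 0.9, so 957 per arm leaves about 861 responders against the plan's own 870 (minor)

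*Protocol article*

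**What the plan says.** The sample size subsection for the quantitative survey (Protocol article) compares two proportions. Control uptake is "5% in the control group and" intervention uptake is 10%, and the text adds that "we assume an increase in the uptake rate of at least five percentage points for the sample size requirement". Allocation is equal (R = "1 for equal allocation") and power is 80% (z = 0.84). The test is described by "For a one-sided test, given the allocation ratio R", with z given as "1.645 for 5% level of significance".

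The base result follows: "The estimated sample size is 435 HCWs in each arm". It is then inflated in a single step: "With a clustering (design) effect of 2 and a 10% non-response rate, a sample size of 957 HCWs is required for each arm". The total given is 3,828, which is 4 × 957. The inflation formula is not written out, and only one non-response rate is given.

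**The concern.** The sentence gives both the loss rate and the resulting sample size, and the two do not agree. If 10% of those approached do not respond, the number to approach is the number of responders needed divided by 0.9. Multiplying by 1.1 always gives too few, because 1.1 × 0.9 = 0.99. The arm then ends 1% below its target whatever the base figure is.

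The figure governs how many health workers are approached in each hospital and what loss the plan can claim to tolerate.

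**Working it through.** **Inputs**, all from the sample size subsection: p1 = 0.05, p2 = 0.10, R = 1, power 80%, base 435 per arm, design effect 2, non-response 10%, final 957 per arm, total 3,828.

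**1. Reproduce the plan's final figure.**
- 435 × 2 = 870 responders per arm after the design effect.
- 870 × 1.1 = 957, an exact match.
- 957 × 4 = 3,828, an exact match.

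**2. Apply the stated non-response to that figure.**
- 957 × (1 − 0.10) = 861.3 responders, against 870 required: about 9 short, or 1.0%.
- Non-response that 957 can absorb: 1 − 870/957 = 9.1%.

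**3. Correct inflation.**
- 870/0.9 = 966.7, rounded up to 967 per arm. Check: 967 × 0.9 = 870.3.
- 967 × 4 = 3,868, which is 10 more per arm and 40 more overall.

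**4. Effect on power**, for a two-sided 5% comparison at a single time, with effective n = responders/2:

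z = [0.05 × √n − 1.96 × √(2 × 0.075 × 0.925)] / √(0.05 × 0.95 + 0.10 × 0.90)

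- 870 responders, n = 435: z = (1.0428 − 0.7301)/0.3708 = 0.843, power 80.1%.
- 861.3 responders, n = 430.65: z = (1.0376 − 0.7301)/0.3708 = 0.829, power 79.7%.

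**5. Where 435 comes from.** With equal allocation, the plan's formula gives a total of

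N = [zα × √(0.075 × 0.925) + zβ × √(0.5 × 0.0475 + 0.5 × 0.09)]² / (0.25 × 0.05²)

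with the power term taken as adding to the first.

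| Test | N with rounded z values | Per arm, rounded z | Per arm, unrounded z |
|---|---|---|---|
| One-sided, z = 1.645 (as stated) | 683.4 | 341.7 | 343 |
| Two-sided, z = 1.96 | 867.9 | 433.9 | 435 |

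The stated 435 is therefore the two-sided result. On the stated one-sided inputs the requirement would be 343 × 2 = 686 responders, and correct inflation would give 686/0.9 = 762.2, rounded up to 763 per arm.

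**The case against.** The strongest reply is that the slip changes nothing in practice. It amounts to 9 responders per arm and 0.4 points of two-sided power. The article also suggests that 957 may be a floor: the study setting section says hospitals were chosen to be large enough for the minimum sample size, and the recruitment section says that all eligible, consenting workers will be enrolled, although it also speaks of approaching randomly selected ones. This stands as to size and is why the point is minor. It does not make the sentence correct.

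A second reply is that 870 is not firmly required. On the one-sided test that the section states, 686 responders suffice, and 861 would give 87.4% power. This also stands. It means that 967 should not be presented as right without saying which test it belongs to. It does not rescue the inflation step, because any base multiplied by 1.1 falls short at 10% non-response.

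A reader might go further and infer that the single allowance covers only one of two contacts, since the planned analysis is a difference in differences and needs a baseline and a later survey. The documents do not support that as a finding. The data collection section says "At the end of the influenza vaccine season, we will do a post-intervention survey at study facilities to collect similar information" but not that the same workers are interviewed again. With two separate samples of 957, one allowance per survey is appropriate. Enrolment and numbered vaccination cards are compatible with a followed cohort but do not settle the matter, and a condensed article may leave it to the full protocol. Any rate for a second loss would be the reader's own assumption. The power of a difference in differences in a cohort would also depend on a within-person correlation that the article does not give.

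**Conclusion.** The arithmetic error is confirmed from the plan's own figures, with no outside assumption: 957 per arm does not leave 870 responders at 10% non-response. The shortfall is about 1%, so the stated size is slightly optimistic but the trial is not endangered by it.

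The figures of 870 and 967 take the base of 435 and the design effect of 2 as the plan gives them. The base is itself unreconciled with the stated test, and the gap between 435 and about 343 is much larger than the inflation slip. The power figures are for the two-sided, single-time comparison that reproduces 435, not for the planned difference-in-differences analysis.

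**What to change.** Correct the sentence in one of two ways:
- keep 957 per arm (3,828 in total) and state that it tolerates 9.1% non-response; or
- restate the size as 967 per arm (3,868 in total) for 10% non-response.

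In the same edit, reconcile the base. If 435 is kept, describe the test as two-sided at 5% with z = 1.96. This agrees with the 95% confidence intervals planned in the data analysis section. If a one-sided test is intended, restate the base as about 343 and recompute the figures that follow from it.

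Keeping 957 costs only the rewording. Moving to 967 means approaching 40 more health workers across the four hospitals.
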